### Study protocol

Figure 2 illustrates the schedule of study procedures and outcome measure assessments. Briefly, within 24 h of enrolment and randomisation, baseline assessments will be completed. These will include ultrasound assessment of muscle and arterial vascular function; blood and urine sample collection and physical function assessment using the ICU mobility score; recording of clinical characteristics such as medical history, diagnosis and severity of illness (assessed using the Sequential Organ Failure Assessment (SOFA) score); documentation of physical function (assessed using the Katz Index of Independence in Activities of Daily Living score) and nutritional status (assessed using the Malnutrition Screening Tool) prior to illness.

**Fig. 2 Fig2:**
[figure not shown]
Schedule of study procedures and outcome measure assessments. DVT deep vein thrombosis, EDTA ethylenediamine tetraacetic acid, ICU intensive care unit, RVOS repetitive vascular occlusion stimulus, SF-12 12-Item Short Form Health Questionnaire

If the participant is randomised to the intervention, one RVOS session will be carried out after baseline assessment on day 1. Arterial blood samples will be collected 3 and 24 h after RVOS and at the same time points after baseline assessments in control participants. From day 2, intervention participants will receive two RVOS sessions per day until day 10 of enrolment or until ICU discharge if this occurs before day 10.

Outcome measure assessments of muscle mass and quality, arterial function, muscle strength, physical function, and blood and urine biomarkers will be repeated on days 6 and 11 of study enrolment. Clinical data including blood results, nutritional and organ support, severity of illness, fluid balance, physiotherapy interventions and specific drug treatment (neuromuscular blocking drugs, corticosteroids, statins and propofol) will be recorded daily from days 1 to 11 of enrolment. At ICU and hospital discharge, physical function and muscle strength assessments will be repeated. In addition, at hospital discharge, an acceptability interview will be conducted with the participant and personal consultee, and blood and urine samples collected. Study participation will end upon completion (by telephone) of the SF-12 health questionnaire 3 months after hospital discharge.

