### Secondary outcome measures

#### Feasibility

Table 3 presents the pre-specified feasibility criteria that will be assessed.

**Table 3 Tab3:** Feasibility criteria of the study

Trial process	Outcome measure	Feasibility criteria
Screening	Percentage of potentially eligible patients being missed	< 55% of potentially eligible patients being missed
Consent	Percentage of personal consultee/participants agreeing to enrolment	> 75% of personal consultees/participants agreeing to enrolment
Recruitment rate	Number of patients recruited	Recruit 30 patients within 16 months
Randomisation	Demographic and severity of illness in the intervention and control arms	Balanced demographic and severity of illness in intervention and control arm participants
Delivery of intervention	Percentage of RVOS sessions performed out of the total possible sessions	80% of the scheduled RVOS sessions performed
Retention rate	Percentage of patients that remain on the ICU for the full 10 days of study enrolment	> 50% of enrolled patients remain on the ICU for the full 10 days of study enrolment
Outcome measure assessments	Percentage of outcome measure assessments performed within 24 h of the scheduled time Percentage of quality-of-life questionnaires completed at 90-day follow-up	100% of RFCSA ultrasound measurements performed within 24 h of the scheduled time > 75% of vascular, strength and functional capacity measures performed within 24 h of the scheduled time > 75% of surviving patients complete the quality-of-life questionnaires at 90-day follow-up
Electronic case report form data collection	Percentage of missing outcome and clinical data	< 10% missing outcome data including ICU and hospital length of stay and survival < 10% missing clinical data obtained from clinical medical notes and electronic patient records, such as severity of illness scores and requirement for organ supportive therapies

*ICU* intensive care unit, *RFCSA* rectus femoris cross sectional area, *RVOS* repetitive vascular occlusion stimulus

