#### Clinical outcomes

Clinical outcomes between participants in the intervention and control arms will be compared: incidence and duration of delirium; incidence, duration and severity of acute kidney injury (assessed using the AKIN classification) [106]; duration of specific organ support (mechanical ventilation, renal replacement therapy, mechanical or pharmacological cardiovascular support); days alive and without a ventilator in the first 28 days of hospital stay; length of ICU and hospital stay; and hospital and 3-month mortality.

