### Data collection and monitoring

All study data will be collected in compliance with the principles of Good Clinical Practice (GCP) and with the Data Protection Act. Patients’ medical notes will be used as source documents for clinical data, while data related to the RVOS intervention (e.g. time of session, cuff pressure, VAS score) and outcome measure assessments will be recorded in a paper workbook before transcribing to a secure web-based electronic data capture system (Promasys) provided by Surrey CTU. The Surrey CTU data management team and sponsor (RSCH) will jointly oversee the administration of study documentation to ensure that study data are authentic, accurate and complete. The sponsor’s Quality and Assurance Officer will conduct monitoring visits to review the source documentation and electronic case report forms (eCRF) and to evaluate them for accuracy, completeness and compliance with the approved protocol, applicable regulations and GCP standards. The frequency of the monitoring visits will depend on the findings of the first patient-monitoring visit at each site.

Participants’ anonymity will be maintained at all times, and study workbooks and other documents will only be labelled with a non-identifiable study participant number. Paper documents that identify participants (such as consent forms) will be stored in a separate folder in a locked office of the secured department site and maintained by investigators in strict confidence. At the end of the trial, any non-essential confidential documents will be destroyed and essential documents will be kept securely for at least 10 years after study completion.

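### The ventilator-free-days outcome counts its 28 days on hospital stay, not from randomisation, so the window can open before treatment and is unclear after a live discharge

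*Protocol article*

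**What the plan says.** In the protocol article, the Clinical outcomes section lists, among the outcomes to be compared between arms, "days alive and without a ventilator in the first 28 days of hospital stay". It gives no other start or end for that count.

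Elsewhere the in-ICU clock runs from enrolment. The Study protocol, RVOS intervention, Muscle mass and quality, and Physical function sections all place sessions or assessments on numbered days of study enrolment.

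Two limits in Table 1 fix how far hospital admission can lie before recruitment. The patient must have entered the ICU within the past 48 h, and more than 48 h in hospital before ICU admission is an exclusion.

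The text under Fig. 2 describes the daily record: "Clinical data including blood results, nutritional and organ support, severity of illness, fluid balance, physiotherapy interventions and specific drug treatment" "will be recorded daily from days 1 to 11 of enrolment". On sources, Data collection and monitoring states that "medical notes will be used as source documents for clinical data", and Table 3 names medical notes and electronic patient records as the source for organ-support requirements.

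The Statistical analysis section limits the between-arm comparisons to direction and size of effect. The Secondary objectives say that clinical outcomes are explored to help power a later trial.

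**The concern.** An outcome meant to show what an intervention does should be counted from the moment the arms can differ, over the same span for every patient. A clock tied to hospital stay fails on both counts.

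- **Start.** Days on the ward or in the ICU before randomisation enter the score although RVOS cannot affect them. An equal number of days at the end of the window drop out. Two patients with the same course after randomisation can then score differently.
- **End.** It is not said how a day after a live discharge counts. On the literal wording it is not a day of hospital stay and earns nothing. Discharge happens after randomisation and may depend on treatment, so this is not baseline noise. If RVOS sped up recovery and discharge, the literal score could move against it.

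At stake is a direction and spread of effect that the investigators intend to carry into the design of the next trial.

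**Working it through.** The plan states no figure that depends on this definition, so there is nothing to reproduce. The check is day-count arithmetic.

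**Inputs**
- Window: 28 days on hospital stay (Clinical outcomes).
- Hospital to ICU admission: at most 48 h (Table 1, exclusion 16).
- ICU admission to recruitment: at most 48 h (Table 1, inclusion 2).
- Daily record: study days 1 to 11 (text under Fig. 2).

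**1. Largest offset before randomisation**

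48 h + 48 h = 96 h = 4 days; 4/28 = 14.3%. A short delay between eligibility and randomisation could add slightly to this.

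**2. What each offset *d* does to the window**

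Post-randomisation days = 28 − *d*. Days after the daily record ends = 28 − *d* − 11.

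| Offset *d* (days) | Share before randomisation | Post-randomisation days | Of these, after day 11 |
|---|---|---|---|
| 0 | 0% | 28 | 17 |
| 1 | 3.6% | 27 | 16 |
| 2 | 7.1% | 26 | 15 |
| 3 | 10.7% | 25 | 14 |
| 4 | 14.3% | 24 | 13 |

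**3. Same course, different score (illustration)**

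Take patients last ventilated on study day 10 who stay alive and in hospital throughout.
- Counted from randomisation: 28 − 10 = 18 for all of them.
- Hospital clock, *d* = 0: 18.
- Hospital clock, *d* = 4: study day 10 is hospital day 14, so 28 − 14 = 14, plus 0 to 4 unventilated days before randomisation. The score is 14 to 18. With two unventilated ward days and two ventilated ICU days it is 16.

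The spread of up to 4 days comes entirely from what happened before randomisation.

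**4. Live discharge (illustration)**

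Take two patients whose last ventilated day is hospital day 8, both alive and unventilated to day 28. Leave aside any unventilated days before ventilation began, taken as equal in both. One goes home on day 12, and one stays in hospital to day 28.
- Literal reading, only hospital days count: 12 − 8 = 4 against 28 − 8 = 20.
- Days after discharge counted: 20 for both.

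**5. Data for a clock from randomisation**

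The daily record covers 11 of 28 days, leaving 28 − 11 = 17 days (61%). For this outcome those days need ventilation start and stop dates and vital status, not daily entries.

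**The case against.** Four days is a ceiling, reached only by a patient at both 48 h limits. At most about two of the four are spent before the ICU. The rest are ICU days in patients who must be on CPAP or invasive ventilation at recruitment, so they need not be ventilator-free. The offset is fixed before randomisation and is therefore balanced between arms in expectation. All of this stands, and it is why the first part is dilution and noise, not bias.

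It can also be said that many analysts would credit days after a live discharge without being told to, so the 4 against 20 contrast rests on a strict reading. That is fair: the article does not say that such days are lost. But its wording points that way, and nothing in it says the opposite.

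A reader might go further and infer that durations of organ support, acute kidney injury and delirium are cut off at day 11, because daily recording ends there and no later organ-support entry is listed. The article does not support this.
- It limits the *daily* record. It does not say that these outcomes are derived only from it, and it names notes and electronic records as the source.
- The same later-visit list also omits "length of ICU and hospital stay; and hospital and 3-month mortality", which are plainly collected, so silence in that list proves little.
- The schedule figure is not available, and an article may leave capture windows to the full protocol.

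Nor does the retention criterion, "> 50% of enrolled patients remain on the ICU for the full 10 days of study enrolment", show that about half the patients would be affected. It is a success threshold for being on the ICU, not a forecast of who is still ventilated or on organ support.

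**Conclusion.** The point holds for one outcome. The 28-day count is stated on the wrong clock: up to about 4 of 28 days (14%) can precede randomisation, and patients get unequal windows of about 24 to 28 days after it. The distribution of offsets is not given, so only the range 0 to 4 days can be stated. The effect is dilution and extra variance.

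The treatment of days after a live discharge is the part that could distort the comparison, since discharge follows randomisation. That rests on the literal reading of the wording, and its size depends on how discharge differs between arms, which is unknown.

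Nothing here shows that the organ-support, kidney-injury or delirium durations are truncated. Length of stay and mortality need only dates and vital status and are untouched. No primary outcome, Table 3 criterion or sample-size figure depends on the 28-day definition. The severity is minor: a secondary, exploratory outcome in a feasibility trial, worth correcting because it is a stated rule, it is cheap to mend, and its result is meant to inform the next trial.

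**What to change.** Define the outcome as days alive and without a ventilator from randomisation (day 1) to day 28, for every patient, counting days alive and off the ventilator after hospital discharge.

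Take ventilation start and stop dates to day 28 from the medical notes and electronic records already used as source, because the daily record reaches only day 11. Vital status after discharge should be available from the 3-month mortality follow-up.

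The Trial status section says recruitment is complete, so the change belongs in the statistical analysis plan, which the article says is signed off before database lock. If lock has already passed, report this version beside the stated one and label it as added later.

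The cost is a few extra dates per patient from existing notes. It needs no new procedure or patient contact and does not change the sample size.

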### Repetitive vascular occlusion stimulus (RVOS) intervention

Participants in the intervention arm will receive one session of RVOS treatment on day 1 and two sessions per day, at least 4 h apart, from day 2 to 10 of study enrolment or until ICU discharge if this occurs before day 10. For safety, the intervention leg will be examined daily before the first RVOS session for deep vein thrombosis (DVT) from the common femoral to popliteal vein using ultrasound (CX50 Philips Ultrasound with L12–3 linear array transducer). If DVT is suspected, RVOS or arterial assessment will not be performed and the clinical team will be notified immediately.

During the RVOS session, the participant will lie supine in a semi-recumbent position with the lower limbs extended. A pressure cuff (SC12LTM segmental pressure cuff; Hokanson, Bellvue, WA, USA) will be applied around the proximal right thigh with a bandage wrapped underneath to avoid skin irritation and bruising. Each RVOS session will last for 40 min and will include four cycles of 5 min cuff inflation to 50 mmHg above the average systolic blood pressure to completely occlude arterial flow distally to the limb [98], followed by 5 min of complete deflation (0 mmHg) (Fig. 3). Pressure in the pneumatic cuff will be controlled by an inflator and air source device (E20 Rapid Cuff Inflator and AG101 Cuff Inflator Air Source; Hokanson). Maximum cuff pressure will be 200 mmHg.

**Fig. 3 Fig3:**
[figure not shown]
Protocol for repetitive vascular occlusive stimulus (RVOS). Each session of RVOS includes four repetitions of 5-min inflation of pneumatic cuff to 50 mmHg supra-systolic blood pressure (SBP) followed by 5 min of complete (0 mmHg) cuff deflation

Vital signs such as blood pressure, heart rate and the saturation of peripheral arterial blood with oxygen will be monitored before and during RVOS, and the session will be terminated if the defined criteria are met (Table 2).

**Table 2 Tab2:** Termination criteria for repetitive vascular occlusion stimulus (RVOS) session

1. Heart rate < 40 bpm or > 180 bpm 2. Systolic blood pressure < 80 mmHg or > 200 mmHg 3. Mean arterial blood pressure < 60 mmHg or > 120 mmHg 4. Peripheral capillary oxygen saturation (SpO_2_) < 88% 5. Pain score > 8/10 on visual analogue scale and unwillingness to proceed with RVOS intervention 6. Objective signs of tissue injury felt due to cuff inflation	

A clinical bedside nurse will be present throughout the RVOS session and will monitor facial expression, limb movement and ventilation compliance for any sign of distress in the sedated participants. In the event that the patient experiences significant discomfort, the cuff pressure will be lowered to a pressure that is tolerated by the participant, and such adjustments will be recorded. If conscious, tolerability of the intervention will be evaluated by asking the participant to rate the pain of the procedure on a visual analogue scale (VAS). After each session, the intervention leg will be examined for signs of arterial insufficiency or tissue injury. In addition, serum creatinine kinase levels will be monitored daily as an indicator of muscle damage.

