### Sample size rationale

A total of 30 participants is recommended for pilot and feasibility trials [97]. To allow for balance in the stratification factors (gender and study site), a sample size of 32 participants was chosen, which will allow us to estimate a failure to deliver RVOS in the intervention arm of 30% to within a 95% confidence interval of ± 15.9%.

Based on an anticipated average rate of recruitment of 6 patients/month, 50% screening failure due to weekends, 20% decline of consent and 30% death before trial completion, we aim to recruit 1.6 patients per site per month. Recruiting from two sites, one starting 2 months after the other, is expected to yield 47 patients over 16 months. Recruitment will continue until 32 ICU survivors have been studied (16 patients in each group).

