#### Tolerability

The VAS pain score will be used to assess the tolerability of RVOS.

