### Statistical analysis

The statistical analysis addresses the objectives of demonstrating the safety and tolerability of applying RVOS to the lower proximal limb of ICU patients, and assessing the feasibility of undertaking a larger-scale study to demonstrate efficacy. As a feasibility trial, the statistical analysis will primarily be exploratory in nature, and thus hypothesis generating rather than confirmatory.

The primary objective of safety will be evaluated based on the frequencies and percentages of adverse events categorised by severity, group and site. The tolerability will be evaluated by assessing VAS pain scores of the intervention arm at each time point in terms of means and standard deviations.

The main feasibility outcome of recruitment will be evaluated as the percentage of randomised participants out of total eligible patients. The number of participants randomised as a percentage of targeted recruitment will also be computed. If data are available, the average number of research assistants’ hours spent on recruiting one participant will also be computed. Retention will be evaluated as the proportion of participants remaining at each time point compared to the number recruited in each arm.

Descriptive statistics will be used to summarise all response variables by site, time point and treatment group. Means and standard deviations will be computed for continuous outcomes and frequencies and percentages will be computed for categorical/dichotomous outcomes. The relationship with potential confounding factors—such as site, demographic data, delirium during ICU stay, severity of illness, length of ICU stay, sepsis (defined using SOFA score), and use of drug treatment (such as corticosteroids, neuromuscular blocking drugs, statins and propofol)—will be explored.

The following inferential statistics will be performed strictly for the purpose of identifying the directions and magnitudes of effects rather than to evaluate the statistical significance of the results due to inadequacy of statistical power.

Outcome measures recorded at a time point (such as ‘timed up and go’ and ‘sit to stand’ assessment) and clinical outcomes (such as duration of mechanical ventilation and length of ICU and hospital stay) will be compared between the two arms using an independent-sample *t* test.

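### A session lowered below systolic pressure can count as RVOS delivered, because neither the 80% delivery criterion nor the pain summary takes account of cuff pressure

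*Protocol article*

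**What the plan says.** **The stimulus.** Under Methods, Repetitive vascular occlusion stimulus (RVOS) intervention, a session is four 5-min inflations to "50 mmHg above the average systolic blood pressure to completely occlude arterial flow distally to the limb", each followed by 5 min of deflation. The legend to Fig. 3 repeats the target. A ceiling of 200 mmHg is set. No floor is set.

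**The response to discomfort.** In the text after Table 2, when a patient has significant discomfort, "the cuff pressure will be lowered to a pressure that is tolerated by the participant, and such adjustments will be recorded". Under Table 2, pain ends a session only if the score exceeds 8/10 and the patient is also unwilling to go on. Loss of occlusion is not a termination criterion.

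**Delivery.** The Table 3 criterion is "80% of the scheduled RVOS sessions performed". The outcome measure beside it is a percentage of all possible sessions. Neither mentions pressure, and the word *performed* is not defined.

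**Tolerability, a primary outcome.** "The VAS pain score will be used to assess the tolerability of RVOS". Statistical analysis will assess "VAS pain scores of the intervention arm at each time point in terms of means and standard deviations".

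**What is recorded.** Data collection and monitoring lists "data related to the RVOS intervention (e.g. time of session, cuff pressure, VAS score" among the workbook items. In the intervention section, "Vital signs such as blood pressure, heart rate and the saturation of peripheral arterial blood with oxygen will be monitored before and during RVOS".

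**Lower-pressure inflation elsewhere.** The Discussion describes repeated inflation at lower pressure as a sham, and withholds it from controls because isolated venous occlusion might do harm.

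**The concern.** The lowering rule is sensible bedside practice in a tolerability pilot. The difficulty is in the counting. A modest reduction from 50 mmHg above systolic still occludes the artery. A reduction to below systolic does not, and what remains resembles the lower-pressure inflation that the Discussion sets apart from RVOS. The delivery criterion cannot tell these sessions apart, and the stated pain summary does not show that the dose was reduced because of discomfort.

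Delivery is central to what the pilot is for. Sample size rationale justifies the number of patients by the precision with which the trial can estimate failure to deliver RVOS. The Discussion makes the larger trial conditional on the pilot showing RVOS to be safe, feasible and acceptable. A delivery percentage that includes non-occlusive sessions would overstate how deliverable the defined stimulus is. A pain mean shown without the reductions behind it would give an incomplete picture of tolerability.

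**Working it through.** **1. The plan's own delivery figure.** Sample size rationale gives ± 15.9% for a 30% failure rate. The half-width is 1.96 × √(0.3 × 0.7 / n). At n = 32 it is 15.88%, which matches. At n = 16, the planned size of the intervention arm, it is 22.5%. That difference is a separate matter, and nothing below depends on it.

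**2. How far the cuff must fall.** Systolic pressure is taken as the limit of occlusion (an assumption, in line with the protocol's supra-systolic target). The starting pressure is the smaller of SBP + 50 and 200 mmHg.

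| SBP (mmHg) | Starting pressure | Margin above SBP | Margin as share of start |
|---|---|---|---|
| 100 | 150 | 50 | 33% |
| 120 | 170 | 50 | 29% |
| 150 | 200 | 50 | 25% |
| 160 | 200 | 40 | 20% |
| 180 | 200 | 20 | 10% |

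Up to SBP 150 it takes a substantial reduction to lose occlusion. Above that, the 200 mmHg ceiling narrows the margin.

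**3. Delivery.** Let p be the share of scheduled sessions performed and s the share of those that are sub-systolic. If *performed* includes lowered sessions, the Table 3 percentage is p whatever s is. Delivery at the defined level of occlusion is p × (1 − s), which equals 0.80 at s = 1 − 0.80/p.

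| Performed (p) | Sub-systolic share that brings delivery down to 80% |
|---|---|
| 100% | 20.0% |
| 95% | 15.8% |
| 90% | 11.1% |
| 85% | 5.9% |
| 80% | 0% |

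Examples: p = 90% and s = 20% give 0.90 × 0.80 = 72%. p = 85% and s = 10% give 0.85 × 0.90 = 76.5%. The criterion as written could read 90% and 85%, both met.

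**4. In sessions (illustrative).** A full course is 1 + 2 × 9 = 19 sessions, so 16 full courses make 304. With 90% performed (274), 31 sub-systolic sessions leave 243, and 243/304 = 79.9%. If 8 of the 16 patients instead leave after day 4 (1 + 2 × 3 = 7 sessions each), the total is 8 × 19 + 8 × 7 = 208. With 90% performed (187), 21 sub-systolic sessions leave 166, and 166/208 = 79.8%. So about 21 to 31 sessions across the arm would change the result.

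**5. Pain score.** If a share f of scored sessions is lowered before scoring, and each then scores d points less, the mean falls by f × d. The documents give neither f nor d. Assuming f = 10% to 20% and d = 2 to 4, the fall is 0.10 × 2 = 0.2 to 0.20 × 4 = 0.8 points. That is 6% to 22% of the mean of 3.6 cited in the Background for another patient group. If patients rate the pain that prompted the lowering, this fall does not occur. The timing is not stated.

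**The case against.** The strongest reply is that the document is silent rather than wrong. *Performed* is undefined, and the Fig. 3 legend describes every RVOS session as having supra-systolic inflations, so a sub-systolic session might be excluded on that reading. A statistical analysis plan is promised before database lock and could define the term and split the pain table. The analysis is described as exploratory, pressure adjustments are recorded, and no stop/go rule hangs on the delivery row alone.

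Much of this stands. A reader might infer that the plan deliberately counts sub-systolic sessions as delivered. The text does not say so; it only leaves that open. But the protocol itself directs the lowering, lets the session continue, and never says that such a session stops counting. The 80% threshold is pre-specified here, and whether it is met should not turn on an unstated reading.

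Three further inferences are tempting but unsupported:

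- **That the pain mean understates pain.** This needs scoring after the lowering, which the protocol does not state. Pain under the lowering rule is also a legitimate measure of tolerability as delivered.
- **That the pain summary biases the decision towards a larger trial.** No pain threshold appears in the document.
- **That sessions kept at full pressure show pain at the defined pressure.** They are selected, because they are the sessions that needed no lowering.

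The Discussion's remark on sham concerns controls, not rescue lowering. It supports the distinction between the two stimuli but does not show harm in treated patients.

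**Conclusion.** The point holds as a weakness in how delivery is counted and tolerability reported. A session lowered below systolic pressure no longer gives the occlusion that defines RVOS, yet it can count as delivered. The 80% criterion can therefore be met with true delivery below 80%, once the sub-systolic share of performed sessions exceeds 5.9%, 11.1% or 15.8% at 85%, 90% or 95% performed. These thresholds are arithmetic. They rest on systolic pressure as the limit of occlusion and on *performed* including lowered sessions.

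Whether the thresholds are reached cannot be judged, since the document gives no expected rate of lowering. Up to SBP 150 the cuff must fall by more than 50 mmHg, and the protocol expects most eligible patients to be sedated, so such sessions may be few. The size and direction of any effect on the pain score are undetermined. This is a cheap improvement worth making; it does not invalidate the pilot.

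**What to change.** **This trial.** Recruitment closed in February 2019 (Trial status), so only the reporting can change.

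- Beside sessions performed, report the percentage of scheduled sessions completed with the cuff kept above systolic pressure, and judge that percentage against 80%. Use the recorded cuff pressures and adjustments, with the session's systolic pressure where it was recorded. The protocol says blood pressure is monitored during sessions. It does not show that a minimum cuff pressure per inflation, or a matching systolic value, was written down. Sessions that cannot be classified should be counted and shown.
- As part of tolerability, give the number and size of pressure reductions alongside the pain means. Flag scores from lowered sessions, without presenting the full-pressure subset as an unbiased estimate of pain at the defined pressure.

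**The larger trial.** State that inflation below systolic pressure does not count as RVOS delivered.

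**Cost.** One derived variable, one extra row in the delivery table and a few lines in the tolerability table. The delivery percentage may come out lower.
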